### Analysis population

The ITT population is defined as all randomised participants with a baseline
measurement. Participants failing to record an outcome value at any follow-up
period will be treated using the methods described below (see “Methods for
handling missing data”).

### Methods for handling missing data

The number of participants with missing observations will be reported for each
outcome variable. Patterns of missing data will be investigated and compared by
demographic characteristics of the participants, t-tests will be used to compare
continuous variables and chi-square tests will be used to compare categorical
variables. For the primary outcome variable (average weekly pain intensity
score) for participants with <10% missing pain intensity values, the missing
pain intensity values will be interpolated using cubic spline interpolation. For
participants with 10% or greater missing data an AUC will not be computed. The
primary method of dealing with missing AUC data will be through multiple
imputation (assuming missing at random), where missing AUC data will be imputed
using the chained equations method of generating a number of complete data sets;
the imputation model will include a range of covariates believed to be
associated with either the missing outcome or the outcome itself (baseline pain
and duration, waiting time, BMI). Sensitivity of analysis results will be
assessed by comparing results obtained various imputation models. If there is
reason to suggest the data may be missing not at random, pattern mixture models
will be utilised^24^.

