#### Primary outcome

The primary outcomes are average weekly back pain intensity (trial one) and
average weekly knee pain intensity (trial two), measured over the course of
follow up.

Participants were asked to report the “average pain intensity experienced in
their back (trial one) or knee (trial two) over the past week, on a 0 to 10
NRS, where 0 was ‘no pain’ and 10 was the ‘worst possible pain’”^6^. These pain intensity scores were measured at baseline, at 2, 6, 10,
14, 18, 22 and 26 weeks. Average weekly (back or knee) pain intensity is
defined as the Area under the Curve (AUC) of the pain intensity trajectory,
over the follow up period. The AUC for each participant will be computed
using the trapezoid rule.

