#### Data collection and follow up

The different stages of data collection and follow-up for secondary outcomes
are summarised in table one. The primary outcome, pain intensity score, was
collected at baseline, week 2, 6, 10, 14, 18, 22 and at 26 weeks. Baseline
assessment was conducted prior to randomisation.

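### With 8 scheduled pain scores the 10% missing-data cut-off admits nobody with a gap: one missed contact removes the computed primary outcome and the planned interpolation can never run.

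*Protocol article*

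**What the plan says.** The article sets out the pain schedule twice. The Primary outcome section reads "These pain intensity scores were measured at baseline, at 2, 6, 10" and continues to week 26. The Data collection and follow up section has pain "collected at baseline, week 2, 6, 10, 14, 18, 22 and at 26 weeks". Both give 8 scores, 7 of them after baseline. Each participant's AUC is computed by the trapezoid rule.

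The section Methods for handling missing data then sorts participants by how much is missing:

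- Below the cut-off: for "participants with <10% missing pain intensity values, the missing pain intensity values will be interpolated using cubic spline interpolation".
- At or above it: for "participants with 10% or greater missing data an AUC will not be computed".

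For the second class, the "primary method of dealing with missing AUC data will be through multiple" imputation by chained equations, assuming missing at random. The AUC itself is imputed, not the missing scores. The covariates are described as "associated with either the missing outcome or the outcome itself (baseline pain" and pain duration, waiting time and BMI). No follow-up pain score is named.

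**The concern.** A percentage cut-off on 8 scores works only if some number of missing scores falls between 0% and the cut-off. Here none does. The authors evidently meant to tolerate small gaps, since they chose a method for filling them, but the rule as written prevents it.

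The primary analysis is what suffers. A participant who misses one call has up to 7 observed scores set aside, and the AUC is replaced by draws from a model whose named predictors are all measured at baseline. That costs precision. It also makes missing-at-random harder to defend: if a missed contact depends on recent pain, the recent scores that would carry this information are not conditioned on. A statistician who finds that the clause cannot operate must either apply it and lose data, or choose another cut-off after seeing the data.

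**Working it through.** **Inputs from the article.** 8 scores, 7 of them follow-up (Primary outcome; Data collection and follow up). Cut-off 10% per participant (Methods for handling missing data). Every ITT participant has a baseline measurement (Analysis population), so any gap is in follow-up. N = 160 and 120 (Participants and recruitment). 15% loss to follow-up, SD 2.3 and 2.7, target differences 1.5 and 2 points, two-sided alpha 0.025 (Sample size).

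**Step 1: can the lower class contain anyone with a gap?** Share missing = k/m.

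| Missing scores k | m = 8 | m = 7 (follow-up only) | Below 10%? |
|---|---|---|---|
| 0 | 0% | 0% | yes |
| 1 | 12.5% | 14.3% | no |
| 2 | 25.0% | 28.6% | no |

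Only complete participants qualify, and they have nothing to interpolate. One gap would fall below 10% only with at least 11 scheduled scores (1/11 = 9.1%).

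**Step 2: how many lose their AUC?** The article gives no miss rate, so the rate p per contact is an assumption, with misses independent. P(no AUC) = 1 − (1 − p)^7. The last column is P(2 or more of 7 missed), the share that would lose the AUC under a rule tolerating one miss.

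| p | As written | Of 160 | Of 120 | One miss tolerated |
|---|---|---|---|---|
| 2% | 13.2% | 21 | 16 | 0.8% |
| 5% | 30.2% | 48 | 36 | 4.4% |
| 10% | 52.2% | 83–84 | 63 | 15.0% |

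Adding 15% dropout: 1 − 0.85 × 0.95^7 = 41%, and 1 − 0.85 × 0.90^7 = 59%.

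**Step 3: how much information is set aside?** Trapezoid weights in weeks are 1, 3, 4, 4, 4, 4, 4, 2 (sum 26, sum of squares 94). Assume equal variances and a common within-person correlation ρ = 0.6, and work in units of the score variance.

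- Var(AUC/26) = 0.6 + 0.4 × 94/676 = 0.656.
- Baseline pain alone: covariance 0.6 + 0.4/26 = 0.615, so R² = 0.615²/0.656 = 58%.
- The 7 observed scores when week 14 is missing: residual variance of that score = 1 − 7 × 0.36/(1 + 6 × 0.6) = 0.452. Its share of the AUC variance = (4/26)² × 0.452/0.656 = 1.6%, so R² = 98%.

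For ρ from 0.4 to 0.8 the comparison is 37–79% against 97–99%.

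**Step 4: cost in precision.** Simulation, 250 runs per cell, ρ = 0.6, 15% monotone dropout plus sporadic misses, with arm included in the AUC-level imputation model. Standard errors are in points of average pain. About 13% of scores are missing at 5% sporadic misses and about 18% at 10%.

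| Trial | Sporadic misses | SE, AUC imputed | SE, scores imputed | Variance ratio |
|---|---|---|---|---|
| One | 5% | 0.338 | 0.298 | (0.338/0.298)² = 1.29 |
| One | 10% | 0.381 | 0.298 | 1.63 |
| Two | 5% | 0.460 | 0.405 | 1.29 |
| Two | 10% | 0.525 | 0.404 | 1.69 |

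The score-level comparator uses the known covariance, so it is slightly optimistic and the ratios lean high. At 2% sporadic misses a smaller run (60 per cell) gave a ratio of about 1.12 to 1.13.

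**The case against.** The arithmetic in Step 1 cannot be disputed. The case on the other side concerns the consequences.

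- *Nobody is excluded.* Every randomised participant with a baseline stays in the ITT analysis through multiple imputation. This stands: what is lost is the computed AUC, not the participant.
- *The covariate list may not be closed.* It is introduced as a range of covariates, the plan promises to compare several imputation models, and pattern mixture models are held in reserve. A statistician could add follow-up scores. But nothing in the text commits to that, and an unspecified sensitivity comparison does not repair the primary estimate.
- *The growth-curve models use all observed scores.* True, but they are secondary analyses.
- *Power remains adequate.* Set against the design targets with z = 2.241 for two-sided alpha 0.025, the AUC-level standard errors give trial one 1.5/0.338 − 2.241 = 2.20 (98.6% power) and 1.5/0.381 − 2.241 = 1.70 (95.5%). Trial two gives 2/0.460 − 2.241 = 2.11 (98.2%) and 2/0.525 − 2.241 = 1.57 (94.2%). All exceed the planned 90%, provided the target difference applies to the whole follow-up average. An effect that emerges late would give less. This stands, and it means the defect does not by itself leave the trials underpowered.
- *No bias has been shown.* Also true. The calculations measure precision, and the weakening of missing-at-random is an argument, not an estimate.

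These points limit how much harm can be claimed. None makes the rule workable.

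**Conclusion.** Wrong as written. That the interpolation clause is empty and that one missed contact removes the computed AUC follow from the article's own schedule and cut-off, whether or not baseline is counted. No assumption is needed.

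The size of the loss does rest on assumptions: independent misses at 2% to 10% per contact, within-person correlation 0.6, and dropout at the 15% allowed for in the sample size. Under these, 13% to 52% of participants lose the AUC through sporadic misses alone. With dropout added and sporadic misses of 5% or 10%, the figure is about 41% or 59%, and the variance is about 1.3 or 1.6 to 1.7 times that of score-level imputation. The demonstrated harm is avoidable loss of precision. Because the rule governs the primary outcome of both trials, it should be corrected before the analysis.

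**What to change.** Delete the 10% rule and the spline step. Impute the individual pain scores for weeks 2 to 26 by chained equations within arm, using all observed pain scores plus the covariates already listed. Compute the trapezoid AUC in each completed data set, then run the planned t-test and pool by Rubin's method as now.

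If interpolation is to be kept, state the cut-off as a count that can operate with 8 scores, and limit it to interior gaps, since a missing week 26 score would need extrapolation. A strict percentage rule would have to exceed 12.5% (8 scores) or 14.3% (7 scores) to admit one gap. Admitting two means accepting 25% of scores filled by single interpolation and should be justified. Participants above the cut-off should still have their observed follow-up scores in the imputation model.

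The cost is revised wording and slightly more programming, with no new data. The article places database lock and analysis in June 2016, after sign-off in May 2016, so on its own timetable the change can be made and dated before lock.

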### Primary analysis

To examine between-group differences in the primary outcome (AUC – based on pain
intensity score) we will use an independent sample Students t-test. The primary
analysis will not adjust for known prognostic variables as covariates, but
results adjusting for these will be presented as a sensitivity analysis (see
below). Separate models will be estimated for each imputed dataset and the means
and standard errors will be combined using Rubin’s method^25^. We will assess other model assumptions (homoscedasticity, normality)
through inspecting appropriate residual plots, where serious violations are
observed we will apply a rank-inverse normal transformation to the pain
intensity score values. Dummy coded variables representing group allocation will
be used to ensure blinding of the analyses. See Table 3 for details.

**Table 3 t03:** Analyses of primary outcome.

**Analysis**	**Outcome**	**Intervention**	**Control**	**Difference**
Primary (ITT Multiple Imputation)	Area under the pain intensity curve (AUC)	mean(95%CI)	mean(95%CI)	mean(95%CI)
Sensitivity	Adjusted AUC*	mean(95%CI)	mean(95%CI)	mean(95%CI)
Secondary	Pain intensity score			
	Baseline	mean(SD)	mean(SD)	
	Week 2,	mean(SD)	mean(SD)	
	Week 6	mean(SD)	mean(SD)	
	Week 10	mean(SD)	mean(SD)	
	Week 14	mean(SD)	mean(SD)	
	Week 18	mean(SD)	mean(SD)	
	Week 22	mean(SD)	mean(SD)	
	Week 26	mean(SD)	mean(SD)	
	Weekly trend	mean(95%CI)	mean(95%CI)	mean(95%CI)

* Adjusted for baseline pain and duration, waiting time, previous
surgery; BMI: physical activity and dietary intake; ITT: Intention
to treat.

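### The stated imputation model for missing AUCs does not name treatment group or the observed follow-up pain scores; if run as listed, it shrinks the primary effect by about the share of AUCs imputed

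*Protocol article*

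**What the plan says.** The Protocol article, under Methods for handling missing data, makes multiple imputation by chained equations the primary way of dealing with missing AUCs: "imputation (assuming missing at random), where missing AUC data will be imputed". On the content of the model it says that "the imputation model will include a range of covariates", described as those "believed to be associated with either the missing outcome or the outcome itself (baseline pain and duration, waiting time, BMI". It gives no other predictor, and it does not mention imputing separately by arm.

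The same section decides who is imputed: for "participants with 10% or greater missing data an AUC will not be computed". The Primary outcome section fixes the number of scores: "These pain intensity scores were measured at baseline, at 2, 6, 10, 14, 18, 22 and 26 weeks", which is eight.

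Under Primary analysis, "we will use an independent sample Students t-test" to compare the groups on AUC, without covariates. "Separate models will be estimated for each imputed dataset and the means" and standard errors are pooled by Rubin's method. Sensitivity to the imputation is to be "assessed by comparing results obtained various imputation models", and those models are not described.

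**The concern.** An imputation model should contain at least every variable in the analysis model. Here the analysis model has one predictor, treatment group, and the imputation text does not name it. Because of randomisation, the four listed baseline variables carry essentially no information about arm. Imputing from them alone therefore draws missing AUCs in both arms from one common distribution, and imputed participants show no treatment difference on average. The pooled estimate moves toward zero, and Rubin's variance, computed under a model that does not match the analysis, is too large. Both errors make a real effect harder to show, and they fall on the primary result of both trials.

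The follow-up scores raise a related problem. Someone who misses one score of eight has no AUC computed, and the listed predictors then ignore the other six follow-up scores. Those scores determine most of that person's AUC and would carry part of the treatment effect into the imputed value.

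**Working it through.** **Inputs from the article (Sample size).** Trial one: SD 2.3, difference 1.5, 80 per group. Trial two: SD 2.7, difference 2.0, 60 per group. Both: two-sided alpha 0.025, 90% power, 15% loss.

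**The plan's own figures.** The article states no imputed share and no bias, so the only figure to reproduce is the sample size. With n = 2·SD²·(2.241 + 1.282)²/difference²:
- Trial one: 2 × 5.29 × 12.41 / 2.25 = 58.4, so 59 per group; 59/0.85 gives 70. The article has 80.
- Trial two: 2 × 7.29 × 12.41 / 4 = 45.2, so 46 per group; 46/0.85 gives 55. The article has 60.

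The stated sizes are larger than these inputs require (power about 0.94 with 68 completers and 0.93 with 51). That is conservative and does not bear on this point.

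**Attenuation if group is not in the model.** Let m1 and m0 be the shares of AUCs imputed in the intervention and control arms, and let the true difference be d. Among observed AUCs the intervention share is p1 = (1 − m1)/(2 − m1 − m0), so imputed values in both arms centre at p1·d above the control mean. Hence

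estimated difference = d·[(1 − m1) + m1·p1] − d·m0·p1 = d·[(1 − m1) + (m1 − m0)·p1].

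With equal shares f this is d·(1 − f). At f = 15%:
- Trial one: 1.5 × 0.85 = 1.275
- Trial two: 2.0 × 0.85 = 1.70

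Unequal missingness changes little: 20% v 10% retains 0.847 of the effect, 30% v 10% retains 0.787, and 40% v 20% retains 0.686.

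**Simulation check.** Proper normal imputation, 10 imputations, 1,500 trials per cell, Rubin pooling with small-sample degrees of freedom, test at two-sided 0.025. Assumed: correlation of AUC with baseline pain 0.5 and with each other covariate 0.1, and missingness completely at random.

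| Trial | Imputed | Estimate without group | Estimate with group | Power without | Power with |
|---|---|---|---|---|---|
| One (true 1.5) | 15% | 1.27 | 1.50 | 0.85 | 0.94 |
| One | 30% | 1.05 | 1.51 | 0.61 | 0.89 |
| One | 50% | 0.76 | 1.50 | 0.17 | 0.72 |
| Two (true 2.0) | 15% | 1.70 | 1.99 | 0.84 | 0.93 |
| Two | 30% | 1.40 | 2.00 | 0.54 | 0.87 |
| Two | 50% | 1.01 | 1.99 | 0.14 | 0.68 |

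**Standard error.** A second simulation built the AUC from repeated scores (assumed correlation 0.6, 250 runs, 20 imputations). For trial one at 40% imputed, the average Rubin standard error without group was 0.342 against an actual sampling standard error of 0.282, a ratio of 1.21. With group included the two agreed (0.338 and 0.350).

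**How large the imputed share could be.** One missed score is 1/8 = 12.5% (1/7 = 14.3% if only follow-ups count). Either exceeds 10%, so any miss leads to imputation. Assuming independent missingness p at each of seven follow-ups, the share imputed is 1 − (1 − p)^7:
- p = 3%: 19%
- p = 5%: 30%
- p = 10%: 52%

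**The case against.** A reader might infer that the plan excludes treatment group and that the primary effect is therefore certain to be shrunk. The text does not go that far. Saying that a model will include a range of covariates does not close the list. The Sensitivity analyses section also lists the same four variables as covariates for the adjusted regression and again does not name group, yet that regression must contain group, since Table 3 reports a between-group difference from it. In this article a covariate list may mean what is added alongside group. An article may also leave the full imputation code elsewhere.

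That makes the finding conditional but does not remove it. The imputation list carries no marker that it is illustrative, although the article uses such markers in its exclusion criteria and under Concomitant treatments. The selection rule it gives does not call for the analysis variables. A programmer following it literally would leave group out. The promised comparison of imputation models could expose the problem, but those models are unspecified and would not change the primary estimate.

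A second tempting inference is that power collapses to below 20%. Those figures need about half the AUCs to be imputed, and only 15% has a basis in the documents. Even there power depends on assumptions: the second simulation gave 96% without group against 98% with it (trial one) and 97% against 99% (trial two), a smaller loss than in the table. It is also fair to say that the bias is toward no effect, so it would not manufacture a benefit.

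**Conclusion.** The point stands in conditional form. The article names only baseline covariates for imputing the primary outcome and states neither that group is included nor that imputation is by arm. If the listed variables are the whole model, the primary effect is attenuated by about the imputed share: roughly 15% at the plan's own loss figure, taking 1.5 points to about 1.27 and 2.0 points to about 1.70, with standard errors too large. The proportional attenuation follows from the algebra when missingness is unrelated to the outcome and covariates are balanced by randomisation, and it hardly depends on the assumed correlations. It takes every lost participant to have an imputed AUC. Larger losses depend on assumed rates of sporadic missingness that the documents do not give, and the power figures are assumption-based throughout. The gain from using follow-up scores was not quantified; it is argued from how the AUC is built.

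**What to change.** State in the missing-data section that dummy-coded treatment group is in the imputation model, or that imputation is done separately within each arm. Because the article already plans dummy-coded allocation for the analysis, the statistician stays blinded.

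Add the observed follow-up pain scores as predictors. A direct way is to impute the missing individual scores and then compute each AUC by the trapezoid rule, so that a participant with one missed score keeps the information from the rest. Group is still needed in that model, since participants lost early have few or no follow-up scores to carry the effect.

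The cost is one line of text and slightly more imputation code. No new data are needed, and the primary outcome and test stay the same.

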### Evaluation of demographics and baseline characteristics

The description of baseline characteristics listed below will be presented by
treatment group. Categorical variables will be summarized by frequencies or
denominators and percentages. Percentages will be calculated using the number of
patients for whom data is available as the denominator. Denominators will be
systematically reported (for example, nn/NN, %). Continuous variables will be
summarised using standard measures of central tendency and dispersion, either
mean and SD, or median and interquartile range.

-Age at randomisation-Gender-Aboriginal and/or Torres Strait Islander-Employment status-Country of origin-Highest level of education-Private health insurance-Other co-existing medical conditions needing medication-Length of time waiting for consultation (days)-Triage classification-Pain intensity and duration-Disability and function-Subjective weight-BMI-Quality of Life-Emotional distress-Sleep quality-Physical activity-Diet-Alcohol consumption-Smoking prevalence-Pain attitudes-Fear avoidance beliefs-Health care utilisation

### Process measures and concomitant treatments

When indicated, data will be summarised per group. Again continuous variables
will be summarised by use of standard measures of central tendency and
dispersion, either mean and SD, or median and interquartile range. Categorical
variables will be summarised by frequencies or denominators and percentages.

### Primary analysis

To examine between-group differences in the primary outcome (AUC – based on pain
intensity score) we will use an independent sample Students t-test. The primary
analysis will not adjust for known prognostic variables as covariates, but
results adjusting for these will be presented as a sensitivity analysis (see
below). Separate models will be estimated for each imputed dataset and the means
and standard errors will be combined using Rubin’s method^25^. We will assess other model assumptions (homoscedasticity, normality)
through inspecting appropriate residual plots, where serious violations are
observed we will apply a rank-inverse normal transformation to the pain
intensity score values. Dummy coded variables representing group allocation will
be used to ensure blinding of the analyses. See Table 3 for details.

**Table 3 t03:** Analyses of primary outcome.

**Analysis**	**Outcome**	**Intervention**	**Control**	**Difference**
Primary (ITT Multiple Imputation)	Area under the pain intensity curve (AUC)	mean(95%CI)	mean(95%CI)	mean(95%CI)
Sensitivity	Adjusted AUC*	mean(95%CI)	mean(95%CI)	mean(95%CI)
Secondary	Pain intensity score			
	Baseline	mean(SD)	mean(SD)	
	Week 2,	mean(SD)	mean(SD)	
	Week 6	mean(SD)	mean(SD)	
	Week 10	mean(SD)	mean(SD)	
	Week 14	mean(SD)	mean(SD)	
	Week 18	mean(SD)	mean(SD)	
	Week 22	mean(SD)	mean(SD)	
	Week 26	mean(SD)	mean(SD)	
	Weekly trend	mean(95%CI)	mean(95%CI)	mean(95%CI)

* Adjusted for baseline pain and duration, waiting time, previous
surgery; BMI: physical activity and dietary intake; ITT: Intention
to treat.

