### Sensitivity analyses

Adjusting for prognostic variables:

The following variables hypothesised to effect outcome will be assessed by their
inclusion as covariates in a linear regression model for the analysis of the
primary outcome (AUC): baseline pain intensity, time since onset of pain,
waiting time, BMI.

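### The primary t-test on pain AUC leaves out baseline pain and so gives up precision, and the adjusted sensitivity model is stated with two different covariate lists

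*Protocol article*

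**What the plan says.** Under Primary analysis, the Protocol article tests the between-group difference in AUC with an unadjusted comparison: "intensity score) we will use an independent sample Students t-test. The primary" "analysis will not adjust for known prognostic variables as covariates"; adjusted results are to be shown as a sensitivity analysis.

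Baseline pain is available for this purpose. Under Data collection and follow up, pain was "collected at baseline, week 2, 6, 10, 14, 18, 22 and at 26 weeks. Baseline" assessment came before randomisation. The Analysis population section limits the intention-to-treat set to randomised participants who have a baseline measurement.

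The adjusted AUC model is described in two places:

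- The Sensitivity analyses section names four covariates: "baseline pain intensity, time since onset of pain, waiting time, BMI".
- The Table 3 footnote reads "Adjusted for baseline pain and duration, waiting time, previous" and continues "surgery; BMI: physical activity and dietary intake; ITT: Intention" to treat. Its punctuation is garbled, but it names seven covariates.

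The section on missing data uses baseline pain and duration, waiting time and BMI as the covariates of the imputation model.

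**The concern.** A participant's pain at entry usually predicts pain over the next six months, and here it is also the first point of the AUC. A comparison that ignores it carries variance that could be removed at no cost in data. It also leaves any chance difference in baseline pain in the estimate, in proportion to the slope of AUC on baseline. The stake is a wider interval for the primary effect than the data require.

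The second matter is consistency. The article presents itself as the pre-determined plan, and two different models cannot both be the planned adjusted analysis. As written, the supporting result in Table 3 is not uniquely defined.

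**Working it through.** **1. The plan's own sample size.** Inputs from the Sample size section: SD 2.3 and difference 1.5 (trial one), SD 2.7 and difference 2 (trial two), two-sided alpha 0.025, power 90%, 15% loss, 80 and 60 per group.

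n per group = 2 × SD² × (2.241 + 1.282)² / difference²

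- Trial one: 59, and 59/0.85 gives 70. The plan states 80.
- Trial two: 46, and 46/0.85 gives 55. The plan states 60.

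The stated numbers are not reproduced exactly, but both exceed what is needed. With 85% retained (68 and 51 per group), power is 94.1% and 93.3%. The unadjusted test therefore meets the stated power.

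**2. Gain from adjusting for baseline pain.** With correlation r between baseline pain and the outcome, the residual variance is multiplied by 1 − r², and the equivalent gain in sample size is 1/(1 − r²). The document gives no r, so 0.3 to 0.7 is an assumption. The planning SDs are used as they stand. They are not stated to be SDs of the AUC.

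| r | variance factor | equivalent sample | trial one: power; difference detectable at 90% | trial two: power; difference detectable at 90% |
|---|---|---|---|---|
| none | 1 | 1 | 94.1%; 1.39 | 93.3%; 1.88 |
| 0.3 | 0.91 | +10% | 96.0%; 1.33 | 95.4%; 1.80 |
| 0.5 | 0.75 | +33% | 98.4%; 1.20 | 98.1%; 1.63 |
| 0.7 | 0.51 | +96% | 99.9%; 0.99 | 99.9%; 1.35 |

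**3. The same question through the visit schedule.** Express the AUC as a weekly average by dividing by 26 weeks. With visits at 0, 2, 6, 10, 14, 18, 22 and 26 weeks, the trapezoid rule gives the baseline score a weight of (2/2)/26 = 1/26, or 3.8%. Assume equal variances and one common correlation between visits of 0.4 to 0.6. The baseline-AUC correlation is then 0.61 to 0.76 and the variance factor 0.63 to 0.42. With 68 and 51 per group, the half-width of a 97.5% interval changes as follows:

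- Trial one: 0.62 to 0.49 points (correlation 0.4), or 0.72 to 0.47 (0.6).
- Trial two: 0.83 to 0.66 points (0.4), or 0.97 to 0.63 (0.6).

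Unadjusted power is above 99% in all four cases, because averaging over visits already shrinks the SD. The gain is in the width of the interval.

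**4. Chance baseline differences.** Under the same assumptions, the slope of AUC on baseline is 1/26 + (25/26) × correlation, which is 0.42 to 0.62. If baseline pain had the planning SD (not stated), the standard error of the baseline difference would be 2.3 × √(2/80) = 0.36 and 2.7 × √(2/60) = 0.49 points. A difference of one standard error would then move the unadjusted estimate by about 0.15 to 0.22 points (trial one) and 0.21 to 0.30 points (trial two). Through the direct weight alone the shift is only 0.36/26 = 0.014 and 0.49/26 = 0.019 points.

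**5. The two covariate lists side by side.**

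| Covariate | Sensitivity analyses | Table 3 footnote | Imputation model |
|---|---|---|---|
| Baseline pain | yes | yes | yes |
| Pain duration / time since onset | yes | yes | yes |
| Waiting time | yes | yes | yes |
| BMI | yes | yes | yes |
| Previous surgery | no | yes | no |
| Physical activity | no | yes | no |
| Dietary intake | no | yes | no |

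Previous surgery appears neither in Table 1 nor in the baseline list under Evaluation of demographics and baseline characteristics. The surgery item in Table 2 is collected at week 26. Physical activity and diet are measured at 0, 6 and 26 weeks and are secondary outcomes that the intervention aims to change. The footnote does not say that baseline values are meant.

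**The case against.** The t-test was chosen openly and in advance. Under 1:1 randomisation it is unbiased, and its interval already allows for chance baseline differences. Power exceeds what the plan claims. Baseline pain is not ignored altogether, since it enters the imputation model and the adjusted sensitivity analysis. All of this stands, and it makes the first part a matter of precision rather than validity.

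Four stronger readings are tempting, and the document does not support them:

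- *Chance imbalance passes in full into the estimate.* It does not. It enters only through the baseline-AUC slope, and the direct weight is 1/26. The planning SDs are not stated to be baseline SDs, and the entry criterion on pain or interference may narrow the baseline spread.
- *The adjusted model could displace the primary test after results are seen.* The plan fixes the unadjusted test as primary and labels the adjusted one a sensitivity analysis. Any choice between lists affects that one row, and the statistician works with dummy-coded groups.
- *Randomisation was not stratified on pain.* The article does not say either way, and it refers to full protocols published elsewhere.
- *The covariate conflict undermines the primary result.* It does not touch it. The Primary analysis section points forward to the Sensitivity analyses section, whose four variables match the imputation model, so the footnote looks like the stray text.

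The footnote is nevertheless part of the plan and contradicts it. And although a correlation range of 0.3 to 0.7 leaves the size of the gain open, adjustment should exclude nobody, because the analysis set requires a baseline measurement.

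**Conclusion.** Both parts hold, at moderate weight. The primary comparison is valid and adequately powered on the plan's inputs, but it gives up precision that is available without collecting anything further. The reduction in residual variance would be 9% to 49% at an assumed baseline-AUC correlation of 0.3 to 0.7. No correlation is given in the document, so the size within that range is uncertain, though the direction is not in real doubt for a repeated pain score. A reader should not infer bias, insufficient power or an undefined primary test.

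The inconsistency between the two covariate lists needs no assumption: three covariates appear in the Table 3 footnote and not in the Sensitivity analyses section. One of them is not in the listed baseline data, and two could be read as post-randomisation values, in which case the model would adjust for something the intervention may have changed. The consequence is confined to the sensitivity analysis.

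**What to change.** Before group codes are revealed:

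1. Make the primary model a linear regression of AUC on arm and baseline pain intensity, fitted in each imputed data set and pooled by Rubin's rules. Report the adjusted difference with its interval.
2. Keep the unadjusted t-test as a sensitivity analysis.
3. For the further adjusted sensitivity model, use the four baseline covariates in the Sensitivity analyses section, which are also those of the imputation model. Correct the Table 3 footnote to match, and state that all covariates are baseline values.

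The data are collected and the regression is already planned, so the analysis work is small. The real cost is procedural. The investigators signed the plan in May 2016, and a change of primary model needs a dated, documented amendment with its reason, made while the analysis is still blind. If group codes have already been revealed, leave the t-test as primary and make only the third change, recorded as a correction.
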